#### Outcome and data collection strategies

A summary of the data collection process is provided in Table 2.

**Table 2 T2:** Data collection process

**Method**	**Data collected**
**Baseline patient visit to Glaucoma Clinic**	
Structured interview	Medical history and social demographics (including: age, gender, IMD, education, employment, marital status, family history of glaucoma)
Baseline Questionnaire (Completed at home)	Satisfaction with Information about Medicines
Resources log	Time spent with GSA (in minutes)
Medical notes	Intraocular pressure measurement

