**Figure 2 F2:**
[figure not shown]
The glaucoma medication adherence model.

● glaucoma and ocular hypertension education requirements identified from the literature and expert clinician advice;

● the Satisfaction with Information about Medicines Scale (SIMS) which has been demonstrated to be a reliable predictor of adherence [49]. SIMS was used to ensure that the BCC template contained the standard information deemed necessary for new glaucoma patients to make an informed decision about use of their ocular hypertensive treatment (travoprost).

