#### The intervention group

In addition to standard care, the intervention group received the BCC intervention following the 10 minute consultation. A telephone advice-line for patients and their carers to respond to glaucoma related queries was also provided by GSAs.

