**Visit 2**	
Visit 2 Questionnaire (Completed at home)	Satisfaction with Information about Medicines
	Morisky Medication Adherence Score
	Frequency of Missed Dose Score
	Possible predictors of adherence. e.g. do you apply your own drops or does somebody help you?
GSA Evaluation Questionnaire (for intervention group only and completed at home)	Satisfaction with Education and Support from GSAs
Resources log	Time spent with GSA (in minutes)
	Time spent with Clinician (in minutes)
Medical notes	Intraocular pressure measurement

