#### Secondary outcomes

Patterns of adherence behaviour: The TDA data were also used to produce graphical representations of adherence in order to classify patterns of adherence behaviour. The methodology and categories described by Ajit et al. in a 3 month study [55] and data on file, were used to classify 5 patterns of adherence; (i) discontinuation of dosing after a short time interval, (ii) adherence ≥ 97%, (iii) adherence < 97% ≥ 80%, (iv) frequent drug holidays, and (v) variable with frequent missed doses.

Medication Possession Ratio (MPR): Upon study completion, computer-generated repeat prescription information was collected from participants’ General Practitioner surgeries. Two MPR calculations were performed to indicate over- or under-usage of eye drop refills during the study; MPRa [38] used the average travoprost drop count [56] and MPRb, used the UK general prescribing instruction to renew eye drop prescriptions every 28 days (Figure 4).

Self-reported adherence: Two self-report adherence measures were utilised, (i) the Morisky Measure of Adherence Score (MMAS) [57] which is a four-item validated measure and (ii) the Frequency of Missed Dose (FMD) which is a measure developed by the authors to quantify the number of eye drop doses missed (once a day, once a week, once a month, or never).

Satisfaction with information received: The validated SIMS was used to quantify satisfaction with information received about travoprost [49].

Patient IOP: Routinely measured and recorded IOP results using Goldmann applanation tonometry were obtained for each eye, at each visit, from the participants’ medical records. The IOP measurement for each treated eye was used to calculate the % reduction in IOP from baseline, visit 2 and 3.

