### Proposed analyses

Descriptive statistics will be used to characterise the demographics of the study population. All analyses will be based on the intention-to-treat principle. Missing data will be imputed using a multivariate normal imputation model after suitable transformations to ensure that the variables are normally distributed. A total of 10 imputed datasets will be created, each analysed separately and the results averaged using Rubin’s equations. The primary analysis will compare the percentage of “adherers” at 8 months post randomisation between intervention and control using chi-squared. Additionally, the combined month 7 and 8 post randomisation adherence score will be analysed using a *t*-test to compare the intervention and control group. A repeated measures analysis-of-variance will be carried out (with time measured in months) to assess for any difference between intervention and control over time.

Secondary analyses will include a sensitivity analysis of the primary analysis by adjusting for any baseline differences and for possible predictive variables (e.g. severity of disease) using logistic regression. SIMS, MPR and IOP change between 8 months and initial visit will be analyzed using a *t*-test to compare the intervention and control group. A reduction in IOP will be correlated with the percentage adherence rate. A correlation between self-reported adherence and the TDA adherence score will be carried out in each arm separately using a Spearman’s correlation coefficient. The self-reported adherence and SIMS scores will be compared both within the control and intervention groups to assess any changes in perceived quality of information given between the baseline, 2 month and end of study visits, as well as between the two groups to compare any differences. No subgroup analyses are planned.

Logistic regression will be used to identify possible adherence predictors. If appropriate, a multivariate model will be constructed to identify independent predictors of adherence.

The difference in total costs and adherence percentage will be calculated incrementally between the intervention and control group to provide the ICER of additional adherence from the intervention. A deterministic sensitivity analysis will be performed on the base case ICER using patient variability in cost and outcome to determine the robustness of the economic analysis. If there is a high degree of uncertainty, the analysis will be bootstrapped.

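### The SIMS labelled baseline is very probably completed after the counselling, so change from it would subtract early benefit; self-reported adherence has no baseline value at all

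*Protocol article*

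**What the plan says.** **Timing of the counselling.** The section on the intervention group states that "the intervention group received the BCC intervention following the 10 minute consultation". Under the baseline clinic visit, Table 2 has the resources log record "Time spent with GSA (in minutes". The health economics section explains that the logged GSA time covers delivery of the counselling and the helpline.

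**Timing and content of the first SIMS.** The same block of Table 2 lists a "Baseline Questionnaire (Completed at home", and SIMS is its only instrument. Under Secondary outcomes, "The validated SIMS was used to quantify satisfaction with information received about travoprost". Participants are newly diagnosed or previously untreated patients who need first-line travoprost (Setting, recruitment and treatment allocation).

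**Self-reported adherence.** Table 2 lists the "Morisky Medication Adherence Score" and the Frequency of Missed Dose score at visits 2 and 3, and not at baseline.

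**Planned analyses.** Proposed analyses says "SIMS, MPR and IOP change between 8 months and initial visit will be analyzed using a" *t*-test between the arms. It adds: "The self-reported adherence and SIMS scores will be compared both within the control and intervention groups to assess any changes". That sentence goes on to name the baseline, 2-month and end-of-study visits, and ends by also planning comparisons between the two groups.

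**The concern.** A change score estimates a treatment effect properly when its starting value was measured before treatment could influence it. Here the starting SIMS seems to be filled in after the counselling, and SIMS is an outcome on which an immediate effect is to be expected. Under Intervention development, "SIMS was used to ensure that the BCC template contained the standard information deemed necessary for new glaucoma patients". If the counselling works as designed, satisfaction with information should rise straight away, and the home questionnaire would record that rise as part of the baseline.

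A change analysis then removes the early benefit instead of measuring it. A successful session could be reported as having no effect on SIMS, or as harmful if satisfaction later drifts back. The within-arm comparison from baseline would likewise miss any immediate gain.

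For self-reported adherence the difficulty is simpler: the analysis text names a time point at which Table 2 collects nothing.

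**Working it through.** **1. Order of events.** The documents give four facts: the counselling follows the initiation consultation; GSA minutes are logged at that visit; SIMS is completed at home; SIMS rates information already received about a drug first started at that visit. A patient could hardly rate that information before the visit. Taken together, the home SIMS follows the counselling in the intervention arm. Nothing in the article places SIMS earlier.

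**2. What the change contrast estimates.** Let D0 be the between-arm effect on SIMS at the home questionnaire and D8 the effect at 8 months. Randomisation removes any other expected difference, so

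E[mean change, intervention − mean change, control] = D8 − D0.

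- D0 = 0 (no early effect): the contrast is D8, as intended.
- D0 = D8 = d (immediate and sustained): d − d = 0.
- D0 = d and D8 = d/2 (fades by half): d/2 − d = −d/2, although the true 8-month benefit is +d/2.

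**3. Size, by illustration.** The documents give no SIMS effect, SD or correlation, so the following are assumptions: D8 = 0.5 SD, equal SDs at both times, and correlation ρ between the two scores of 0.3 to 0.7. The 81 per arm comes from the sample size section. That figure belongs to the primary outcome; it reproduces closely (81 per group at 60% against 80% gives 79.9% power, two-sided 5%) and serves here only as a plausible analysed number.

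With f the share of the 8-month effect already present at the home questionnaire:

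- contrast = 0.5 × (1 − f)
- SE = √(2 − 2ρ) × √(2/81)
- power = Φ(|contrast|/SE − 1.96) + Φ(−|contrast|/SE − 1.96)

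Example with f = 0.5 and ρ = 0.5: contrast 0.25, SE = 1 × 0.157 = 0.157, ratio 1.59, power 36%.

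| f | Expected contrast (SD) | Power, ρ = 0.3 | ρ = 0.5 | ρ = 0.7 |
|---|---|---|---|---|
| 0 | 0.500 | 77% | 89% | 98% |
| 0.25 | 0.375 | 52% | 67% | 87% |
| 0.5 | 0.250 | 27% | 36% | 54% |
| 0.75 | 0.125 | 10% | 13% | 18% |
| 1 | 0 | 5% | 5% | 5% |
| 1.25 | −0.125 | 10% | 13% | 18% |

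In the last row the rejections fall mostly in the wrong direction. Comparing the 8-month scores alone has 89% power whatever f is (0.5/0.157 = 3.18; Φ(3.18 − 1.96) = 0.89).

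**4. Within-arm change.** In the control arm it estimates the time trend; in the intervention arm, the trend plus D8 − D0. Neither contains D0, so an immediate effect is invisible in both.

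**5. Self-reported adherence.** The analysis names baseline, 2 months and end of study. Table 2 offers visits 2 and 3 only, and patients not yet treated have no travoprost adherence to report. What can be computed is visit 2 against visit 3 within arms, and arm against arm at each.

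**The case against.** **The order is not stated.** True. It is put together from several sections, and the pathway figure might show something else. The inference is strong because of what SIMS asks, but it remains an inference.

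***Change* may attach to IOP alone.** In the *t*-test sentence this is a fair reading. Secondary outcomes defines a reduction from baseline only for IOP and computes MPR once, at study completion. A reader might infer that the plan wrongly calls for a change in MPR. The documents do not support that as an error, since the absence of an initial MPR value itself favours the narrower reading. For SIMS the ambiguity matters, and the later sentence names baseline in any case.

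**Between-arm comparisons are already planned.** Correct, and they are valid without a pre-intervention score. A reader might infer that the plan cannot detect an effect on SIMS; it can. The remaining problem is that the plan does not make these comparisons the main SIMS result and calls the first score a baseline, so conflicting results could be reported with no rule on which one counts.

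**Cancellation is not inevitable.** Also correct. It needs an effect that is immediate and neither grows nor fades. The helpline runs throughout and GSA time is logged at visits 2 and 3, so later gains are possible and would survive in a change score.

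**The self-report wording may be loose.** The three time points follow a phrase about perceived quality of information, which fits SIMS better than adherence. That makes it a wording error that no analyst could carry out wrongly. It still needs correcting, because self-reported adherence is a subject of the same sentence.

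**Conclusion.** The point holds for the change-from-baseline analyses of two secondary outcomes.

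- **SIMS.** The first score is very probably post-intervention in the counselled arm. If it is used as the starting value, the between-arm contrast is D8 − D0. The loss can range from none to complete, with reversal if the effect fades. Under the assumed 0.5 SD, power falls from 89% for a direct 8-month comparison to 27% to 54% when half the effect is early, and to the 5% error rate when all of it is. The algebra needs only the inferred order; the power figures rest on assumed SIMS values.
- **Self-reported adherence.** The baseline time point has no data under Table 2.

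The primary analysis of adherence recorded by the dosing aid is unaffected. This should be corrected, but it does not threaten the trial's main conclusion.

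**What to change.** Amend the wording of Proposed analyses and the label in Table 2:

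1. Call the home SIMS the first post-intervention measurement, and do not use it as a baseline or covariate.
2. Make the between-arm comparison of SIMS scores at each time point the SIMS analysis, with 8 months as the main one, adjusted for the two stratification factors (diagnosis and experience of the glaucoma service). The home questionnaire then serves as the estimate of early effect.
3. Keep within-arm SIMS changes only as a description of durability, not as evidence of effect.
4. Limit the Morisky and missed-dose comparisons to visits 2 and 3.
5. State that *change* in the *t*-test sentence applies to IOP only, and that MPR is compared as a single whole-study value.

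Data collection does not change. The downside is that the SIMS analysis has no pre-intervention score to adjust for. Little is given up, because before the visit patients have received next to no information about travoprost to rate.

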**Visit 2**	
Visit 2 Questionnaire (Completed at home)	Satisfaction with Information about Medicines
	Morisky Medication Adherence Score
	Frequency of Missed Dose Score
	Possible predictors of adherence. e.g. do you apply your own drops or does somebody help you?
GSA Evaluation Questionnaire (for intervention group only and completed at home)	Satisfaction with Education and Support from GSAs
Resources log	Time spent with GSA (in minutes)
	Time spent with Clinician (in minutes)
Medical notes	Intraocular pressure measurement
**Visit 3**	
Visit 3 Questionnaire	Satisfaction with Information about Medicines
	Morisky Medication Adherence Score
	Frequency of Missed Dose Score
	Possible predictors of adherence. e.g. do you apply your own drops or does somebody help you?
Resources log	Time spent with GSA (in minutes)
	Time spent with Clinician (in minutes)
Medical notes	Intraocular pressure measurement
**Duration of study**	
Resources log	Time spent with GSA on help-line telephone calls
Evaluation of TDA data	Percentage adherence score using TDA
Prescription data capture	Repeat prescription count

#### Primary outcome measure

Adherence magnitude: Participant adherence to travoprost, was measured using the TDA. Participants were provided with written operating instructions [48] and shown how to use the TDA, including how to replace an empty bottle with subsequent supplies. Participants were asked to use the TDA to administer their travoprost eye drops for the study duration. The primary outcome measure was the average number of doses administered over the monitoring period, recorded by the TDA, and percentage adherence calculated using the adjusted adherence calculator [48] (calculation as in Figure 4). Adherence was calculated for the total study duration and for 8 separate monthly periods to explore trends throughout follow-up. Additionally, a binary classification of adherence score was used (‘adherent’ if the average number of TDA recorded doses is ≥ 80% of expected and ‘non-adherent’ if < 80%).

**Figure 4 F4:**
[figure not shown]
Calculations used for outcome measures; Adherence % and Medication Possession Ratios (a and b).

#### Secondary outcomes

Patterns of adherence behaviour: The TDA data were also used to produce graphical representations of adherence in order to classify patterns of adherence behaviour. The methodology and categories described by Ajit et al. in a 3 month study [55] and data on file, were used to classify 5 patterns of adherence; (i) discontinuation of dosing after a short time interval, (ii) adherence ≥ 97%, (iii) adherence < 97% ≥ 80%, (iv) frequent drug holidays, and (v) variable with frequent missed doses.

Medication Possession Ratio (MPR): Upon study completion, computer-generated repeat prescription information was collected from participants’ General Practitioner surgeries. Two MPR calculations were performed to indicate over- or under-usage of eye drop refills during the study; MPRa [38] used the average travoprost drop count [56] and MPRb, used the UK general prescribing instruction to renew eye drop prescriptions every 28 days (Figure 4).

Self-reported adherence: Two self-report adherence measures were utilised, (i) the Morisky Measure of Adherence Score (MMAS) [57] which is a four-item validated measure and (ii) the Frequency of Missed Dose (FMD) which is a measure developed by the authors to quantify the number of eye drop doses missed (once a day, once a week, once a month, or never).

Satisfaction with information received: The validated SIMS was used to quantify satisfaction with information received about travoprost [49].

Patient IOP: Routinely measured and recorded IOP results using Goldmann applanation tonometry were obtained for each eye, at each visit, from the participants’ medical records. The IOP measurement for each treated eye was used to calculate the % reduction in IOP from baseline, visit 2 and 3.

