### Rationale for sample size calculations

The absence of an accepted adherence rate with once daily glaucoma medication [7] and limited research to indicate the likely effect of an intervention led to estimates being derived from general medicine. In general medicine, average non-adherence rates of 25% have been reported [62] with interventions achieving an average 35% adherence increase [23]. Reports of glaucoma adherence studies using medication monitors, have had shorter follow-up time and more complicated dosing regimens than the proposed study [63,64]. Therefore, without a comparable study, a 20% increase in adherence was estimated for sample size power calculations with adherence defined as ≥ 80% of expected doses recorded by TDA. Assuming an adherence rate of 60% in the control group and 80% in the intervention group, 81 people in each group provides 80% power to detect a difference using a Chi-Squared test, at a 5% level of significance. Based on an estimated 20% drop-out rate, a target was set of 200 participants.

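### The IOP outcome is defined as % reduction per treated eye but tested as unadjusted change: settle one scale and one value per patient, and adjust for baseline IOP

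*Protocol article*

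**What the plan says.** All references are to the protocol article.

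- **Data.** Under Secondary outcomes, routine IOP readings "were obtained for each eye, at each visit, from the participants’ medical records". Table 2 lists "Intraocular pressure measurement" at the baseline visit and again at visits 2 and 3.
- **Outcome definition.** The same section states "The IOP measurement for each treated eye was used to calculate the % reduction in IOP from baseline, visit 2 and 3". The scale is a percentage and the unit named is the treated eye.
- **Arm comparison.** Under Proposed analyses: "SIMS, MPR and IOP change between 8 months and initial visit will be analyzed using a *t*-test to compare the intervention and control group". No covariate is named for IOP.
- **Association.** The same section adds "A reduction in IOP will be correlated with the percentage adherence rate". Under Primary outcome measure, adherence is one score per participant.
- **Adjustment elsewhere.** Covariates enter only a "sensitivity analysis of the primary analysis by adjusting for any baseline differences and for possible predictive variables", by logistic regression. That concerns adherence, not IOP.
- **Stratification.** Randomisation was stratified by diagnosis and by experience of the glaucoma service (Setting, recruitment and treatment allocation). Neither factor appears in the IOP analysis.

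**The concern.** Three things in these passages do not fit together well.

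First, the outcome is defined as a percentage reduction and tested as a change. These are different variables with different variances, and they can give different p-values from the same readings.

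Second, the definition is at eye level, while the t-test and the correlation both need independent observations and adherence exists only per patient. Nothing says how a patient with two treated eyes contributes.

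Third, baseline IOP enters only by subtraction or division. As a covariate it would give a more precise arm difference from the same data.

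IOP is the only clinical measure among the listed secondary outcomes, and the Background says that adherence and clinical endpoints should ideally both be assessed. A difference between arms, or an association with adherence, would be read as clinical support for the intervention. The result should not depend on an unstated choice of scale or unit.

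**Working it through.** **The plan's own figure.** No figure is given for IOP. The only sample size is for the primary outcome: "Assuming an adherence rate of 60% in the control group and 80% in the intervention group", 80% power, 5% level (taken as two-sided). With pooled variance and no continuity correction:

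n = [1.96·√(2·0.7·0.3) + 0.842·√(0.24 + 0.16)]² / 0.2² = 81.2 per arm

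The plan states 81; rounding up gives 82. Power at 81 per arm is 79.9%. Allowing for 20% drop-out, 162/0.8 = 203, against a target of 200. The figure reproduces, and nothing below changes it.

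**Precision lost without baseline adjustment.** Let r be the correlation between baseline and 8-month IOP. The article gives no value, so 0.3 to 0.7 is assumed, with equal SDs σ at both times.

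- Change-score variance: 2σ²(1 − r)
- ANCOVA residual variance: σ²(1 − r²)
- Ratio: (1 − r²) / [2(1 − r)] = (1 + r)/2

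The ratio is 0.65, 0.75 and 0.85 at r = 0.3, 0.5 and 0.7, so ANCOVA has 35%, 25% and 15% less variance.

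This ratio applies to absolute change, not to % reduction. To compare all three, an illustrative simulation (4,000 runs) used 81 patients per arm with one value each, baseline mean 26 (SD 4), follow-up mean 19 (SD 3.5) and an arm difference of 1.5 mmHg. All the IOP values are assumptions. Power was:

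| r | t-test, change | t-test, % reduction | ANCOVA |
|---|---|---|---|
| 0.3 | 58% | 69% | 82% |
| 0.5 | 70% | 82% | 87% |
| 0.7 | 90% | 96% | 96% |

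At r = 0.5 the choice between the plan's two scales alone moves power by 12 points. The gain of ANCOVA over % reduction is 13 points at r = 0.3, 5 at r = 0.5 and almost none at r = 0.7.

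**Type I error if eyes were entered separately.** Let s be the share of patients with two treated eyes and ρ the between-eye correlation of the outcome. The article gives neither, so s = 0.5 to 1.0 and ρ = 0.3 to 0.9 are assumed.

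- Design effect: D = [(1 − s) + 2s(1 + ρ)] / (1 + s)
- Actual error of a nominal 5% test: 2·[1 − Φ(1.96/√D)]

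| s | ρ | D | Type I error |
|---|---|---|---|
| 0.5 | 0.3 | 1.20 | 7.4% |
| 0.5 | 0.5 | 1.33 | 9.0% |
| 0.75 | 0.7 | 1.60 | 12.1% |
| 1.0 | 0.8 | 1.80 | 14.4% |
| 1.0 | 0.9 | 1.90 | 15.5% |

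An eye-level correlation with adherence would face the same problem, because both eyes of a patient carry the same adherence score. With one value per patient, or a model with a patient effect, the error returns to 5%.

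**The case against.** The strongest case against has four parts.

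- **Unit.** A reader might infer that patients with two treated eyes are counted twice. The article does not say so. It describes how a percentage is derived, not what is entered in the test. The paragraph is labelled as patient IOP, IOP shares its t-test sentence with two patient-level measures, and averaging the eyes or choosing one fits the text. A condensed article may also leave that rule to a fuller document. This stands, so the type I error figures are conditional.
- **Baseline.** A reader might infer that baseline IOP is wasted, or that regression to the mean biases the comparison. Neither holds. Baseline is the reference for both the percentage and the change, and under randomisation regression to the mean affects both arms alike in expectation. The unadjusted test is valid; only precision is lost.
- **Size.** The (1+r)/2 ratio overstates the gain if % reduction is the variable tested, as the simulation shows. This also stands.
- **Scale.** Change may be shorthand for the % reduction defined earlier. That is possible, but the sentence describes a difference between two time points and does not mention a percentage. Both versions are printed, so condensation does not explain the mismatch.

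IOP is also one of several secondary outcomes, and the Background notes that there is no universal standard for using it to measure adherence. That limits the weight of the point, but the improvement is still worth making.

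**Conclusion.** The point holds as a free improvement to a secondary outcome. The article names two IOP scales and fixes an unadjusted t-test although baseline IOP and the stratification factors are already available. The test is valid but inefficient: ANCOVA needs 65% to 85% of the change-score variance for an assumed r of 0.3 to 0.7 with equal SDs, and its advantage over % reduction may be smaller.

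The unit of analysis is left open. Type I error of about 7% to 16% would arise only if eyes were entered as separate observations, and that range rests on assumed values of s and ρ. The documents do not support saying that this will happen. The primary comparison and the sample size are untouched.

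**What to change.** In Proposed analyses:

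1. Define one IOP value per patient at each visit as the mean of the treated eyes, with baseline taken over the same eyes. Alternatively, keep eye-level data in a mixed model with a patient effect.
2. Name one scale for the test, for example 8-month IOP in mmHg, and use the same term in Secondary outcomes.
3. Estimate the arm difference at 8 months by ANCOVA on baseline IOP and the two stratification factors, with a confidence interval.
4. Use the patient-level value in the correlation with adherence.
5. Report % reduction alongside.

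The cost is a change of wording, with no new data, visits or patients. Because it settles the scale of a stated secondary outcome, it should be recorded and dated before IOP is compared by arm.
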